# A Model for Empowering Rural Solutions for Cervical Cancer Prevention (He Tapu Te Whare Tangata): Protocol for a Cluster Randomized Crossover Trial

**DOI:** 10.2196/51643

**Published:** 2023-09-14

**Keywords:** uterine cervical neoplasms, cervical intraepithelial neoplasia, early detection of cancer, papillomavirus infections, New Zealand, self-testing, primary health care, Indigenous people, Māori, point-of-care systems, colposcopy, health equity

## Abstract

**Background:**

Māori are the Indigenous people of Aotearoa (New Zealand). Despite global acceptance that cervical cancer is almost entirely preventable through vaccination and screening, *wāhine* Māori (Māori women) are more likely to have cervical cancer and 2.5 times more likely to die from it than non-Māori women. Rural Māori residents diagnosed with cervical cancer have worse outcomes than urban residents. Living in rural Aotearoa means experiencing barriers to appropriate and timely health care, resulting from distance, the lack of community resourcing, and low prioritization of rural needs by the health system and government. These barriers are compounded by the current screening processes and referral pathways that create delays at each step. Screening for high-risk human papillomavirus (hrHPV) and point-of-care (POC) testing are scientific advances used globally to prevent cervical cancer.

**Objective:**

This study aims to compare acceptability, feasibility, timeliness, referral to, and attendance for colposcopy following hrHPV detection between a community-controlled pathway and standard care.

**Methods:**

This is a cluster randomized crossover trial, with 2 primary care practices (study sites) as clusters. Each site was randomized to implement either pathway 1 or 2, with crossover occurring at 15 months. Pathway 1 (community-controlled pathway) comprises HPV self-testing, 1-hour POC results, face-to-face information, support, and immediate referral to colposcopy for women with a positive test result. Pathway 2 (standard care) comprises HPV self-testing, laboratory analysis, usual results giving, information, support, and standard referral pathways for women with a positive test result. The primary outcome is the proportion of women with hrHPV-positive results having a colposcopy within 20 working days of the HPV test (national performance indicator). Qualitative research will analyze successes and challenges of both pathways from the perspectives of governance groups, clinical staff, women, and their family. This information will directly inform the new National Cervical Screening Program.

**Results:**

In the first 15-month period, 743 eligible HPV self-tests were performed: 370 in pathway 1 with POC testing and 373 in pathway 2 with laboratory testing. The positivity rate for hrHPV was 7.3% (54/743). Data collection for the second period, qualitative interviews, and analyses are ongoing.

**Conclusions:**

This Māori-centered study combines quantitative and qualitative research to compare 2 clinical pathways from detection of hrHPV to colposcopy. This protocol draws on rural community practices strengths, successfully engaging Māori from a *whānau ora* (family wellness) approach including *kanohi ki te kanohi* (face-to-face), *kaiāwhina* (nonclinical community health workers), and multiple venues for interventions. It will inform the theory and practice of rural models of the use of innovative technology, addressing Māori cervical cancer inequities and facilitating Māori wellness. The findings are anticipated to be applicable to other Indigenous and rural people in high-income countries.

**Trial Registration:**

Australian New Zealand Clinical Trials Registry (ANZCTR) ACTRN12621000553875; https://anzctr.org.au/Trial/Registration/TrialReview.aspx?ACTRN=12621000553875

**International Registered Report Identifier (IRRID):**

DERR1-10.2196/51643

## Introduction

### Background

Māori are the Indigenous people of Aotearoa (New Zealand). *He Tapu Te Whare Tangata* reflects the veneration of *wāhine* Māori (Māori women) and people with cervices as sacred *whare tangata* (houses of humanity) from a Māori worldview [1]. The overall name of this project “He Tapu Te Whare Tangata—a model for empowering rural solutions” affirms the importance of women’s right to best health.

*Whānau* (families) living in rural Aotearoa face barriers to appropriate and timely health care. This is a complex issue involving distance from main centers, the lack of community resourcing, and low prioritization of rural needs by the national health care system and government. Residents of rural areas have poorer health outcomes than those living in urban areas, and for Māori, who experience inequities in access to care, social determinants of health, and quality of care, this is accentuated [2-4]. To address these barriers, effective solutions for rural Aotearoa should involve both innovative technologies and community empowerment. Using the cervical cancer screening pathway, this partnership project pairs innovative technology with community control of the care pathway to reduce barriers to timely care.

Cervical cancer is one of the few cancers preventable through both vaccination and screening. Screening can detect precancer of the cervix that can be treated, halting the development of a potentially fatal outcome. *Wāhine* Māori are twice as likely to have cervical cancer and 2.5 times more likely to die from it than non-Māori women [5]. Māori living in rural areas diagnosed with cervical cancer have worse outcomes compared with urban residents [6]. These cancers disproportionately affect young *wāhine* Māori and are the second leading cause of cancer death for *wāhine* Māori aged 25-44 years [7,8]. These inequities are unacceptable and are caused by barriers to screening, diagnosis, and treatment [9].

Most cervical cancers occur in women who have not undergone screening or are screened less frequently [10]. The National Cervical Screening Program (NCSP) shows that the target level of 80% of *wāhine* Māori screened within the previous 3 years is not achieved in any region; once screened, there is a failure to achieve a timely diagnosis and treatment of abnormalities for *wāhine* Māori [9]. Fewer *wāhine* Māori have a colposcopy within an appropriate time frame following a high-grade abnormality when compared with non-Māori women. Furthermore, the proportion of women who had no record of any subsequent follow-up at 90 days is 4.4% for European women but 8.6% for *wāhine* Māori [11].

The current national screening approach for cervical cytology involves an invasive procedure using a speculum, which requires attending a clinic with associated transport and other costs. Cervical screening in rural Aotearoa is performed by the primary care nurse or physician, and the tests are sent to a centralized laboratory for analysis. The results are returned to the primary care clinician, who then notifies the patient. If the result is abnormal, the clinician writes a referral letter to a gynecologist requesting an appointment for a colposcopy. Hospital departments then control all further investigations and treatments. Delays can occur at each point, which in turn create barriers to access, timely diagnosis, and treatment [12].

Human papillomavirus (HPV) is the causative agent of cervical cancer. Infection with certain oncogenic (cancer forming) high-risk types of HPV cause changes in the cells of the cervix that can lead to cancer. Compared with cytology, HPV-based screening is a better test; it provides 60% to 70% greater protection against developing invasive cervical cancers [13,14]. The World Health Organization recommends that all countries transition to HPV testing as the primary method for cervical screening [15-17]. It is also internationally recognized that a self-taken swab that uses molecular amplification testing platforms such as polymerase chain reaction is as effective in detecting high-risk HPV (hrHPV) as a clinician-taken sample [18,19].

The present cytology-based NCSP is changing to HPV primary testing this year [20]. HPV self-testing is an equitable tool for cervical screening. Increasing coverage with HPV self-testing will potentially contribute to a more equitable NCSP [20]. A recent randomized controlled trial found that offering an HPV self-test was almost 3 times more likely to result in a cervical screen for underscreened *wāhine* Māori compared with offer of conventional cervical cytology [21]. Qualitative research has shown that HPV self-testing is highly acceptable to *wāhine* Māori, although many who had a positive result felt that more information and support were needed to guide them through the colposcopy process [1,22].

Point-of-care (POC) technology enables on-site HPV testing of self-collected vaginal swabs. The Xpert HPV test by Cepheid has been clinically validated to detect infections with 14 hrHPV types (16, 18, 31, 33, 35, 39, 45, 51, 52, 56, 58, 59, 66, and 68) that are likely to be associated with cervical disease (eg, cervical intraepithelial neoplasia 2+). The Xpert HPV test differentiates between HPV16 and HPV18/45, which are linked to approximately 70% of cervical cancers. The 14 hrHPV types assessed by the Xpert HPV test are associated with >90% of cervical cancers, as demonstrated in a recent Australian study [23]. The sensitivity and specificity of the Xpert HPV test are comparable with those of other well-established HPV central laboratory-based assays and fulfill the World Health Organization’s criteria for use [19,24].

The research center Te Tātai Hauora O Hine (The National Centre for Women’s Health Research Aotearoa, Victoria University of Wellington) was invited to partner with the Iwi (tribal) group Ngāti Pāhauwera Development Trust (NPDT) and Māori health provider Ngāti Porou Oranga (NPO, previously Ngāti Porou Hauora) to try a new clinical pathway for colposcopy using HPV self-taken vaginal swabs, POC testing, and direct referral to secondary services. In the early stages, Tipu Whaipua, a Wairoa-based community steering group formed through a prior research project with NPDT, helped inform the development of the design [25], which was guided by the principles of Ngāti Pāhauwera—*Pakatō i te ata, Pakatō i te ahiahi, Maure mahi Māuri ora* (planning for the future health and well-being of the people) and *Mahia nga māhi o Kahukura* (imagining and creating a better future).

NPO is a Māori primary health organization; it is the sole provider for a challenging geographic area, with a flourishing research and innovation program. The vision of the late [name] was “for Ngāti Porou Hauora to lead our own research, as a tikanga (traditional, customary way) and research-based centre of excellence for Hauora Māori” [26]. These principles provided the foundation for this research partnership and the resulting study, “He Tapu Te Whare Tangata—a model for empowering rural solutions.”

This study combines a cluster crossover intervention trial with qualitative work to address inequities in the clinical care pathway to colposcopy for *wāhine* Māori in rural Aotearoa. This study pairs HPV self-testing with POC technology in a novel community-controlled cervical cancer prevention pathway. This easy-to-use technology with a 1-hour turnaround provides quick results for women *kanohi ki te kanohi* (face-to-face) and the ability to provide immediate woman-centered care, including information, *manaakitanga* (support), *whānau* (family) involvement, and shared decision-making. This, in turn, allows for immediate referral to colposcopy appointments for follow-up of positive tests.

### Objectives

The objectives of this study are as follows: (1) to compare 2 pathways of care on the timeliness, referral to, and attendance for colposcopy following hrHPV detection (quantitative) and (2) to assess the acceptability and feasibility of the 2 cervical cancer prevention pathways (qualitative).

## Methods

### Overview

This is a cluster randomized crossover trial, with 2 primary care health practices (study sites) as clusters. Each site was randomized to implement either pathway 1 or pathway 2 in the first study period (15 months) and then crossing over to implement the other pathway in the second study period (15 months). The trial design is summarized in Figure 1.

Pathway 1 is HPV self-testing and POC results within 1 hour, with face-to-face information, support, and immediate referral to colposcopy for women with a positive test result for hrHPV—the community-controlled pathway.

Pathway 2 is HPV self-testing and laboratory analysis, followed by usual results giving, information and support, and standard referral pathways for women with a positive test result for hrHPV—the current standard pathway.

We hypothesize that pathway 1 will improve timely access to colposcopy compared with pathway 2.

We hypothesize that community control of the care pathways is acceptable and feasible for rural Māori communities.

This study is informed by the Kaupapa Māori inquiry paradigm. This paradigm sees being Māori as normal and challenges how Māori have been, and continue to be, constructed within a colonized worldview. It promotes a structural analysis of inequities for Māori, seeking to more fully understand people’s lives and the systemic determinants of their health and wellness [27,28]. In this paradigm, Māori worldviews, ways of knowing, and *mātauranga* Māori (Māori knowledge) are seen as valid and legitimate.

Non-Māori colleagues working collaboratively in a strengths-based approach are included in the team, which is Māori led [29]. With this Māori-centered approach led by *Kaumātua* (Māori elders and knowledge holders), we seek to combine multiple ways of knowing and seeing the world. Māori are involved at all levels, including protocol development, instigation, follow-up, and trialing of this innovative clinical care pathway [25]. Research practices reflect *tikanga* Māori (Māori customs), including the importance of place, relationships, and Māori self-determination [26,27].

The 2 rural North Island community primary health care practices are in Hawke’s Bay and Tairāwhiti on the East Coast of the North Island of Aotearoa at sites A and B, respectively. These 2 primary health care providers serve a predominantly rural and Māori population. The Hawke’s Bay practice is based in 1 health center in a rural town covering an area of approximately 4000 km^2^. The Tairāwhiti practice includes 5 clinics situated in small rural communities, covering a coastline of >200 km.

**Figure 1 figure1:**
[figure not shown]
He Tapu Te Whare Tangata—a model for empowering rural solutions: study design. HPV: human papillomavirus; hrHPV: high-risk human papillomavirus; POC: point-of-care. *Eligible women: women aged 24.5 to 69.9 years due or overdue for cervical cytology.

### Outcomes

The primary outcome is the proportion of women having a colposcopy within 20 working days from the test, for those women with a positive test result for hrHPV.

Secondary outcomes are of those with a positive hrHPV test result:

Proportion of women having a colposcopy within 40 working days of the testProportion of women having a colposcopy within 20 working days of referralProportion of women having a colposcopy within 40 working days of referralTime from test to colposcopyTime from referral to colposcopyNumber of high-grade lesions (cervical intraepithelial neoplasia and carcinoma)Planned treatment for women with high-grade histology at colposcopy.

Secondary outcomes include of all women taking the HPV test:

The proportion of women who test positive for hrHPVThe proportion of women who test negative for hrHPVThe proportion of women who have invalid resultsThe proportions due for screening, underscreened, or never screened.

Qualitative outcomes are as follows:

To explore and understand the successes and challenges of both pathways from the perspectives of the governance groups, clinical staff (nurses, doctors, *kaiāwhina* [nonclinical community health workers], and specialists), and women (including *whanau* or family supporters) at both sitesTo understand this new screening pathway to advise and inform a more culturally responsive NCSP.

On the basis of the percentage reported for *wāhine* Māori throughout Aotearoa, we estimated that 56.4% of women in the control arm will have a colposcopy within 20 working days following referral for a positive HPV test [30]. We aim to detect a 50% increase (relative risk 1.5) from 56.4% to 84% in the primary outcome for the intervention arm. A sample size of 80 women (n=40, 50% in each arm) in a 2-period, 2-cluster randomized crossover trial will provide 80% power at 2-sided α of .05 to detect a 50% increase in the intervention arm. With only 2 practices serving as the clusters, the sample size does not account for the cluster effect, which will be considered as a fixed effect in the final analysis.

The order of treatment for each practice has been randomly allocated by the study statistician using computer-generated random numbers. Using the eligible population list for each practice, the research team randomly allocated half of the under- or never-screened women to priority recruitment in the first study period and half to the second study period. This was done to reduce the potential bias from unequal recruitment of under- or never-screened women between the 2 study periods. The lists for priority recruitment were provided to the practices.

As this is a 2-period, 2-cluster randomized crossover trial, each practice acts as a comparator for the other practice during the trial period.

Blinding of participants and clinicians is not possible. The 2 trial statisticians will be unblinded and compile the data set and conduct the statistical analysis.

The inclusion criteria were women aged 24.5-69.9 years eligible for cervical screening in these 2 rural areas. In line with the current NCSP protocol, women can present for the first screen up to 6 months before their 25th birthday and be included. Women can present for screening up to 6 months before their due date and be included [31]. Women who are due for screening or who are underscreened (underscreened is defined as never screened or ≥4 years since last screening) are eligible.

Women with heavy bleeding at the time or those using a vaginal cream that might interfere with the test are asked to return at a later date. Women who opt for cervical cytology or whose general practitioner advises a speculum examination and cervical cytology can also participate in the study by taking an HPV self-taken (or clinician taken) swab first. Women who have symptoms such as abnormal bleeding can still be offered an HPV test, but they will also be seen and assessed by a general practitioner and may require assessment by secondary gynecology services despite a negative hrHPV test.

Primary care clinicians (physicians and nurses) and *kaiāwhina* at both sites received training from the research team on how to obtain informed consent from women. Training was conducted in person or via a video link. Trained clinicians or *kaiāwhina* obtain informed consent from women in both pathways for a copy of their HPV results (and if colposcopy is required, copies of histology results) to be sent to the researchers and the ordering health practitioner.

Women are also asked if they can be contacted later by a qualitative researcher for an interview on their experiences of the pathways (pathway 1 or 2, the HPV self-test, and overall process) and any subsequent follow-up. Other key stakeholders from general practice (management and staff) and the wider community have been identified and invited to participate in an interview.

Physicians, nurses, and *kaiāwhina* at both sites received an HPV update and information sharing session with the research team before recruitment started. These updates included the role of HPV in cervical cancer, the HPV self-test, the role of POC testing, how to obtain informed consent, how to instruct women on taking a self-taken swab, how to follow-up results, the role of the research team, and how the study will run. Training is augmented by regular ongoing contact between the research team, clinic staff, and managers.

All eligible women in both pathways are offered an HPV self-test. The participants receive verbal, written, and pictorial instructions from a physician, nurse, or *kaiāwhina* on how to self-collect a vaginal sample using a nylon-flocked swab (Copán FLOQswabs). Most sample collection takes place at the primary care practice, but some women self-collect the sample in their homes during a *kaiāwhina* visit or take one home from the clinic. Women in pathway 1 are provided information about POC testing. Women in both pathways who have positive HPV results are offered usual support to attend colposcopy. This includes petrol vouchers, transportation, and a support person to accompany them.

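### The sample size rests on a control rate timed from referral (56.4%), while the primary outcome is timed from the HPV test, so the stated 80% power is not shown for the primary outcome

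*Protocol article*

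**What the plan says.** The Outcomes section of the protocol article defines the endpoint thus: "The primary outcome is the proportion of women having a colposcopy within 20 working days from the test", among women who test positive for high-risk HPV. The abstract starts the clock at the same point. The list of secondary outcomes then includes, as a separate item, colposcopy within 20 working days counted from referral.

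The sample-size paragraph in the same section takes its control rate from a national figure ("On the basis of the percentage reported for *wāhine* Māori throughout Aotearoa") and estimates that "56.4% of women in the control arm will have a colposcopy within 20 working days following referral for a positive HPV test". The next sentence moves this number to the primary outcome: "We aim to detect a 50% increase (relative risk 1.5) from 56.4% to 84% in the primary outcome for the intervention arm". The resulting size is "A sample size of 80 women (n=40, 50% in each arm"), which the article says "will provide 80% power at 2-sided α of .05 to detect a 50% increase in the intervention arm".

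The Pathway 2 section places several steps between test and referral: transport to the laboratory, analysis, electronic return of the result to the clinician, and a referral letter. Under Pathway 1 the result takes about an hour and the colposcopy appointment is made at once by telephone. No section gives the length of the test-to-referral interval in either pathway.

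**The concern.** The control rate belongs to one endpoint and the power claim to another. The article itself treats the two as different, because it lists the referral-timed proportion separately as a secondary outcome.

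The difference matters in this trial. Shortening the time between test and referral is a central part of what pathway 1 does. A control rate timed from referral leaves that interval out of standard care, whereas the primary outcome counts it.

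What is at stake is the meaning of the stated 80% power and of the target effect (56.4% to 84%). A reader of the final report who takes the 80% as the power for the primary outcome would be relying on a calculation done for a different quantity. The reader also could not tell which effect on the from-test scale the trial was sized to detect. The definition of the primary outcome, its analysis and the type I error are not affected.

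**Working it through.** **Inputs from the Outcomes section:** control rate 56.4%, relative risk 1.5, 40 women per arm, two-sided alpha 0.05, power 80%, no allowance for clustering.

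**Step 1. Reproduce the stated size.** I used the two-proportion formula with pooled variance under the null and no continuity correction:

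n per arm = [1.96 × √(2p̄(1−p̄)) + 0.842 × √(p1(1−p1) + p2(1−p2))]² / (p2−p1)²

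- With p1 = 0.564 and p2 = 1.5 × 0.564 = 0.846, n = 39.9, rounded up to 40 per arm. Power at 40 per arm is 80.1%.
- With p2 = 0.84 as printed, n = 42 per arm and power at 40 is 78.1%. With unpooled variance the same inputs give n = 39.2, rounded up to 40, and 80.8% power.

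The arithmetic is sound, and it uses the referral-timed rate.

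**Step 2. Compare the two clocks.** Referral follows the test. A woman seen within 20 working days of her test has therefore also been seen within 20 working days of her referral, but not the reverse. In the same women, the from-test rate is at most the from-referral rate. The two are equal only if the interval is zero or no woman's colposcopy falls between the two deadlines. With laboratory and letter steps in pathway 2, a zero interval is implausible.

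**Step 3. Show how much it could matter.** The article gives no lag, so everything in this step is an assumption made for illustration. Let waiting time after referral be exponential with 56.4% seen by day 20, and let the pathway 2 test-to-referral lag be L working days:

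λ = −ln(1 − 0.564)/20 = 0.0415 per day; from-test control rate = 1 − exp(−λ(20 − L))

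For L = 5 this is 1 − exp(−0.0415 × 15) = 46%. Power at 40 per arm then depends on which feature of the planned effect is held fixed:

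| Lag L (working days) | Control rate | Power, RR 1.5 kept | Power, 27.6-point gain kept | Power, pathway 1 at 84% | RR if pathway 1 at 84% |
|---|---|---|---|---|---|
| 3 | 51% | 66% | 74% | 90% | 1.7 |
| 5 | 46% | 56% | 72% | 96% | 1.8 |
| 7 | 42% | 46% | 71% | 99% | 2.0 |
| 10 | 34% | 33% | 70% | >99% | 2.5 |

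The 27.6 points are 84% − 56.4%. Power falls steeply in the first case, modestly in the second, and rises in the third.

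**The case against.** The strongest reply is that 56.4% is an external national estimate and not this trial's own control rate. Both pathways offer petrol vouchers, transport and a support person, and the population is rural, so the trial's rate on either clock could lie above or below the national one. This stands. The ordering in Step 2 holds within the same women and does not prove that the trial's from-test rate is under 56.4%.

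A second reply is that the low power figures come from assumed lags and from holding the relative risk at 1.5. At a lag of 10 days that puts pathway 1 at 0.34 × 1.5 = 51%. In the same model, removing the lag alone would bring pathway 1 to 56.4%, so the 33% figure describes an implausibly weak intervention. This also stands. A reader might infer that the trial is underpowered, but the documents do not support that. Pathway 1 nearly removes the interval, so it could reach a rate near 84% on the from-test clock, and power would then be higher than stated.

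Third, the words about referral may be loose phrasing for a rate counted from the test. That would not rescue the sentence as printed, because the same section keeps the two clocks apart.

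Three further inferences are tempting and should not be drawn.

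- The abstract describes the outcome as "having a colposcopy within 20 working days of the HPV test (national performance indicator"), which might suggest that the label is on the wrong outcome. How the indicator is defined depends on a cited source that is not at hand.
- The Background says "The present cytology-based NCSP is changing to HPV primary testing this year", which might suggest that the 56.4% comes from women referred on cytology. That raises a question about the source but shows no error.
- A reader might expect the result to be benchmarked against 56.4%. No section plans this. The figure is only a planning input, and the comparison is between randomised pathways.

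**Conclusion.** The mismatch is real and can be read within a single section. The 80 women and 80% power are derived from a referral-timed control rate and then attributed to a test-timed primary outcome, so the power for the primary outcome has not been shown. This conclusion needs no assumption beyond the article's own wording and the reproduced calculation (40 per arm, 80.1%).

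The size and direction of the consequence are undetermined. Over the illustrative lags of 3 to 10 working days, power at 40 per arm runs from 33% to over 99%, depending on whether the relative risk, the absolute gain or the pathway 1 rate is held at its planned value. Those figures rest on the assumed lags, on exponential waiting, and on taking 56.4% as the trial's own referral-timed rate. They show that the from-test target effect needs to be stated. They do not show that the trial is too small.

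**What to change.** Reword the sample-size paragraph, and carry the same wording into the final report:

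- State that 56.4% is timed from referral and so corresponds to the secondary outcome of colposcopy within 20 working days of referral.
- Give a control rate timed from the test, either sourced or openly assumed with a range. If none is available, label 56.4% as an approximation or upper bound for the primary outcome. The lags used above are illustrations and should not be adopted as planning values.
- Restate the target effect and the power on the from-test clock, under both the relative risk of 1.5 and the absolute difference.
- Do not repeat the 80% figure as the power for the primary outcome.

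The cost is a change of wording and a less certain statement of power. The endpoint and the analysis stay as they are, and no extra women are needed.
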